#### 2.3.2. Secondary Outcomes

The secondary outcomes include: optimization of E2 and LH levels; optimization of menstrual cycle length; change in BMI level; improvement in quality of life using the FSFI questionnaire; and comparing the effectiveness between the 3 study groups.

### 2.4. Sample Size

A parallel, 3-group design will be used. We determined the sample size using G*Power 3.1.9.7 software. We employed one-way analysis of variance (ANOVA) due to consideration of three different therapies. The effect size was estimated at 0.4. We set alpha to 0.05 and power to 0.95. Consequently, the software provided an estimated total sample size of 102, resulting in 34 cases per group. To account for a potential dropout rate of 15%, we increased the sample size to 40 participants per group. Therefore, the total sample size needed for the study is 120 participants [31].

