### 2.3. Objectives

The primary objective of this study is to assess the efficacy of specific exercise routine on ovarian function compared with a standard of care and low intensity walking in patients with diminished ovarian reserve, by optimizing hormone levels for better stimulation possibilities.

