### 2.5. Statistical Methods

Descriptively, we intend to calculate the mean, standard deviation, minimum, maximum, and range of data, while the occurrence of spontaneous pregnancy will be presented as a percentage. For the evaluation of results, after conducting the Shapiro–Wilk normality test, paired T-tests or Wilcoxon tests will be used to compare baseline and three-month laboratory results within each group, and one-way analysis of variance (ANOVA) or Kruskal–Wallis’s test, along with Tukey’s post hoc test, will be used for comparison among the three groups. Chi-square tests or Fisher’s exact tests are planned to be applied for comparing the numbers or percentages between groups.

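### The 0.95 power belongs to the overall three-group F test; exercise versus walking, half of the objective, is reached only through all-pairs Tukey, and its power is not given

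*Protocol article*

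**What the plan says.** Section 2.3 of the protocol article states the primary objective as "to assess the efficacy of specific exercise routine on ovarian function compared with a standard of care and low intensity walking". With Arm A as the standard-care arm, that is two contrasts: C versus A and C versus B.

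Section 2.4 bases the sample size on the overall test only: "We employed one-way analysis of variance (ANOVA) due to consideration of three different therapies". The inputs are an assumed effect of 0.4, a 5% significance level and a target power of 95%. The reported result is that "the software provided an estimated total sample size of 102, resulting in 34 cases per group", raised to 40 per group for 15% dropout. It names no pairwise difference and no pattern of group means.

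Section 2.5 plans ANOVA or Kruskal–Wallis, "along with Tukey’s post hoc test, will be used for comparison among the three groups". Section 2.3.2 lists a comparison of the three groups among the secondary outcomes, and 2.6 tells participants that three groups will be compared.

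**The concern.** The overall F test can reject because any arm differs from any other, for instance because both active arms differ from A, with nothing shown about exercise against walking. Its power is therefore not the power of either comparison in the objective. Tukey's test also spends part of the 5% error on B versus A, and with only three groups it is stricter than family-wise control requires.

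What is at stake is mainly how a null result is read. Section 5 presents the trial as the first to compare this programme with walking and with no activity. A non-significant C versus B result, read beside a stated power of 0.95, invites the conclusion that the programme is no better than walking, when the trial may have had a modest chance of showing a real difference.

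**Working it through.** **Inputs from 2.4:** k = 3 groups, effect size 0.4 (read as Cohen's f, the software's ANOVA input), alpha 0.05, 34 evaluable per arm, 102 in total.

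**Step 1, the plan's own figure.** Non-central F with df = (2, N − 3) and non-centrality N·f².
- N = 99: power 0.949.
- N = 102: non-centrality 102 × 0.16 = 16.32, critical F(2, 99) = 3.088, power 0.955.

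So 102 is the smallest balanced total that reaches 0.95. Dropout: 102 / 0.85 = 120. Both stated figures are right.

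**Step 2, what f = 0.4 means for a pair (assumption).** f is the SD of the three group means divided by the within-group SD. It does not fix any one pairwise difference. Let the means of A, B and C be proportional to (0, L, 1), where L is the share of the exercise effect that walking also gives, and scale them to f = 0.4.

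Example, L = 1/2: the SD of (0, 0.5, 1) is 0.408, so C − A = 0.4 / 0.408 = 0.980 SD and C − B = 0.490 SD.

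**Step 3, pairwise power.** Non-central t with pooled df = 99 and non-centrality d·√(34/2). Critical values are 2.379 for Tukey (studentized range divided by √2) and 1.984 unadjusted. For L = 1/2, the non-centrality for C versus B is 0.490 × √17 = 2.02, below Tukey's 2.379, and the power is 36%.

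The last two columns come from simulation: unadjusted pairs after a significant F test, and the fixed sequence C versus A then C versus B.

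| L | d, C vs B | Overall F | C vs A, Tukey | C vs B, Tukey | C vs B, F then unadjusted | C vs B, fixed sequence |
|---|---|---|---|---|---|---|
| 0 | 0.849 | 95% | 87% | 87% | 92% | 89% |
| 1/3 | 0.641 | 95% | 94% | 61% | 74% | 74% |
| 1/2 | 0.490 | 95% | 95% | 36% | 51% | 51% |
| 2/3 | 0.321 | 95% | 94% | 15% | 26% | 26% |

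Overall power stays at about 95% in every row while C versus B power falls from 87% to 15%. With all 40 per arm retained, the Tukey figures for C versus B are 92%, 69%, 43% and 18%.

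**Step 4, error control of unadjusted pairs after a significant F test.** If all three means are equal, nothing is tested unless F rejects, which happens 5% of the time. If exactly two are equal, only one pairwise null is true, and it is tested at 5%. If all differ, no false rejection is possible. With three groups, the family-wise error is therefore at most 5% within one outcome.

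**The case against.** The strongest reply is that nothing in 2.4 is false. It names the ANOVA as the basis and never attributes 0.95 to a pair. ANOVA followed by Tukey is a valid plan, and it serves the three-group comparison in 2.3.2 and 2.6. All of this stands. A reader might infer that the sample size is wrong or that the trial claims 95% power against walking. The documents support neither.

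The range also rests on a pattern of means that the plan does not give. A reader might take 15–87% as the trial's power for C versus B. It holds only if walking gives between none and two thirds of the exercise effect with f held at 0.4. Other patterns run from about 2% (walking equals exercise, so there is no difference to find) to about 95% (walking as far below standard care as exercise is above it). C versus A, the other half of the objective, is well powered throughout.

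Dropping B versus A to save power would not be free, given 2.3.2 and 2.6. The remedy below therefore keeps that test. No choice of pairwise test cures low power if walking has a substantial effect: at d = 0.490, 80% power for one unadjusted contrast needs 2(1.960 + 0.842)² / 0.490² ≈ 66 per arm.

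What survives is a mismatch between the objective and the hypothesis that was powered, together with a pairwise test stricter than three groups require.

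**Conclusion.** The point holds as an inexpensive improvement to a stated method, not as an error in the sample size. The 0.95 is correct omnibus power and is not the power of either comparison in the objective. Under the stated assumptions (f = 0.4, 34 per arm, one normal outcome, walking giving 0 to 2/3 of the exercise effect), Tukey leaves C versus B at 87% down to 15%. Unadjusted pairs after a significant F test gain about 5 to 15 percentage points at the same 5% family-wise error per outcome. The gain is real but does not bring C versus B to 80% once walking gives a third or more of the effect, so stating the power openly matters as much as changing the test.

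**What to change.** 1. **Section 2.5.** For each continuous primary outcome keep the ANOVA. If the overall F test is significant at 0.05, test the pairwise differences at unadjusted two-sided 0.05 in place of Tukey. Name C versus A and C versus B as the comparisons of interest. B versus A keeps its test.
2. **Alternative.** A fixed sequence, C versus A at 0.05 and then C versus B at 0.05 if the first is significant. Its C versus B power is about 89%, 74%, 51% and 26%, at the price of the formal B versus A test.
3. **Section 2.4.** Say that 0.95 is the power of the overall test, and give the C versus B power beside the assumed share of the effect that walking provides.
4. **Reporting.** Give C versus B with a confidence interval, so that a non-significant result is not read as equivalence to walking.

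**Cost.** Wording only, with no added patients. The stated power for the key comparison becomes less favourable, and Tukey's simultaneous intervals are given up. The 5% control applies within one outcome. Section 2.3.1 names FSH change, AMH change and spontaneous pregnancy as primary, and multiplicity across them is not addressed by this change.

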### 2.5. Statistical Methods

Descriptively, we intend to calculate the mean, standard deviation, minimum, maximum, and range of data, while the occurrence of spontaneous pregnancy will be presented as a percentage. For the evaluation of results, after conducting the Shapiro–Wilk normality test, paired T-tests or Wilcoxon tests will be used to compare baseline and three-month laboratory results within each group, and one-way analysis of variance (ANOVA) or Kruskal–Wallis’s test, along with Tukey’s post hoc test, will be used for comparison among the three groups. Chi-square tests or Fisher’s exact tests are planned to be applied for comparing the numbers or percentages between groups.

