### 2.1. Study Setting

This study will involve women aged 20–42 diagnosed with diminished ovarian reserve (DOR) who meet the following criteria: (1) AMH levels < 1.1 ng/mL at the beginning of the cycle, (2) BMI between 18.5 and 30 kg/m^2^, (3) regular and normal menstruation, and (4) specified hormone levels (TSH < 2.5 mIU/mL, vitamin D3 > 75 nmol/L, Prolactin < 24 ng/mL). We plan to enroll 120 patients between January 2025 and December 2025.

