#### 2.3.1. Primary Outcome

The primary outcome is the change in FSH and AMH levels compared with the levels before. Spontaneous pregnancy during the study period will be recorded as a primary outcome measure.

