### 4.6. Baseline Assessments

Baseline assessments will adhere to the trial’s standard operating procedure (SOP). During the first visit, between days 2 and 4 of the cycle, a laboratory examination will be conducted, including hormone levels of AMH, FSH, LH, E2, PRL, TSH, 25-OH-D3 vitamin, and progesterone. Baseline progesterone will be measured between days 21 and 22 of the same cycle. The FSFI questionnaire will also commence during this phase.

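### The between-arm test is picked by a normality pretest, Tukey's test is attached to Kruskal–Wallis as well as to ANOVA, and the comparison is not adjusted for baseline AMH and FSH

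*Protocol article*

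**What the plan says.** - **Choice of test (section 2.5).** The plan reads: "after conducting the Shapiro–Wilk normality test, paired T-tests or Wilcoxon tests will be used to compare baseline and three-month laboratory results within each group". The same sentence goes on to ANOVA or Kruskal–Wallis between groups, so the normality result selects the between-arm test too.
- **Post hoc test (section 2.5).** "Kruskal–Wallis’s test, along with Tukey’s post hoc test, will be used for comparison among the three groups". As worded, Tukey accompanies either omnibus test. No rank-based follow-up is named.
- **Outcome (section 2.3.1).** "The primary outcome is the change in FSH and AMH levels compared with the levels before". Section 2.5 does not say whether the between-arm test uses this change or the 3-month value.
- **Baseline data (section 4.6).** On cycle days 2–4 of the first visit, "a laboratory examination will be conducted, including hormone levels of AMH, FSH, LH, E2, PRL, TSH, 25-OH-D3 vitamin, and progesterone". Section 2.5 names no covariate and no transformation.
- **Entry limit (section 2.1).** "AMH levels < 1.1 ng/mL at the beginning of the cycle", which cuts off the upper end of baseline AMH.
- **Sample size (section 2.4).** "We employed one-way analysis of variance (ANOVA) due to consideration of three different therapies", with "The effect size was estimated at 0.4", alpha 0.05 and power 0.95, giving 102 patients, raised to 120.

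**The concern.** There are three linked weaknesses in rules that the article states.

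1. **The method is not fixed.** ANOVA compares means and Kruskal–Wallis compares rank distributions. If the data choose, AMH and FSH may be analysed on different scales, and no single effect measure is set in advance.
2. **The pairing is wrong.** Tukey's test relies on normality and equal variances. The Kruskal–Wallis branch is entered because normality was rejected, so Tukey would be applied where its premise has just been set aside. The objective in section 2.3 (exercise against standard care and against walking) is answered by these pairwise results, and there is no rule for an omnibus and a pairwise result that disagree.
3. **Precision is given away.** Baseline AMH and FSH are available for every patient but do not enter the between-arm model as covariates.

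**Working it through.** **Step 1: the plan's own figure.** One-way ANOVA with 3 groups, f = 0.4 and alpha 0.05 has noncentrality N·f² and N − 3 error degrees of freedom.
- N = 99: 99 × 0.16 = 15.84, power 94.9%.
- N = 102: 102 × 0.16 = 16.32, power 95.5%.

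So 102 is the smallest balanced total, and 34/0.85 = 40 per arm gives 120. The stated sample size is reproduced.

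**Step 2: variance by method.** Take equal variance σ² at baseline and at 3 months, with correlation r:
- 3-month value alone: σ²
- change score: 2σ²(1 − r)
- ANCOVA: σ²(1 − r²)

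ANCOVA relative to change is (1 − r²)/[2(1 − r)] = (1 + r)/2. Relative to the 3-month value it is 1 − r². The documents give no r, so a range is shown. The last two columns take f = 0.4 to apply to the scale named and allow one degree of freedom for the covariate; power is to be compared with 95.5%.

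| r | ANCOVA/change | ANCOVA/3-month | ANCOVA power at N = 102, f on change | Same, f on 3-month value |
|---|---|---|---|---|
| 0.3 | 0.65 | 0.91 | 99.6% | 97.0% |
| 0.5 | 0.75 | 0.75 | 98.9% | 98.9% |
| 0.7 | 0.85 | 0.51 | 97.8% | 99.9% |
| 0.9 | 0.95 | 0.19 | 96.4% | >99.9% |

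**Step 3: the pretest strategy against log-ANCOVA.** Simulation with 34 per arm, log-normal AMH, log SD 0.6, baseline cut at 1.1 ng/mL and Group C raised by 0.3 log units (6000 runs). All of these except the arm size and the cut are assumptions. Omnibus rejection rates:

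| Generating r | Pretest, 3-month values | Pretest, change | Log-ANCOVA |
|---|---|---|---|
| 0.3 | 0.54 | 0.48 | 0.58 |
| 0.5 | 0.56 | 0.60 | 0.68 |
| 0.7 | 0.61 | 0.79 | 0.84 |
| 0.9 | 0.68 | 0.996 | 0.998 |

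With no effect, all three stayed between 0.046 and 0.053 (the two pretest strategies between 0.047 and 0.053). The entry limit lowers the correlation actually seen: a generating r of 0.7 became about 0.61–0.62 on the log scale. All three arms passed Shapiro–Wilk in 0.2–12% of runs on 3-month values and in 9–30% on change scores. Under these assumptions Kruskal–Wallis is the branch usually taken.

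A second simulation with other assumed effects gave a similar picture for pretest on change against log-ANCOVA: 0.60–0.61 against 0.69–0.71 at r = 0.5, 0.81 against 0.85–0.86 at r = 0.7, and above 0.99 for both at r = 0.9.

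**Step 4: Kruskal–Wallis followed by Tukey.** Kruskal–Wallis was significant with no significant Tukey pair in about 0–8% of trials on change scores and up to about 9% on 3-month values in one set of assumptions. Another set used 3-month values, 34 per arm, no entry cut and only Group C shifted (8000 runs):

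| Log SD | Shift in C | Kruskal–Wallis significant | Of all runs: no Tukey pair | Of all runs: Tukey pair, Kruskal–Wallis not significant |
|---|---|---|---|---|
| 0.6 | +0.3 | 52.1% | 10.1% | 6.4% |
| 0.6 | +0.5 | 93.5% | 4.7% | 1.8% |
| 0.8 | +0.3 | 30.9% | 11.2% | 6.0% |
| 0.8 | +0.5 | 72.3% | 14.3% | 4.9% |

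In the two +0.3 rows, 10.1/52.1 = 19% and 11.2/30.9 = 36% of significant Kruskal–Wallis results had no pair to explain them. Tukey's own familywise error with no effect was 4.5–5.2%.

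**The case against.** The strongest defence has five parts.

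- **Baseline is in the outcome.** Section 2.3.1 defines the primary outcome as a change, and section 4.7 repeats this. A reader might infer from section 2.5 that baseline is ignored; the documents do not support that. What stands is that the between-arm comparison is not adjusted for baseline and that its variable is left unnamed.
- **No invalidity is shown.** A reader might infer that the pretest or the Tukey pairing inflates false positives. The simulations show rates near 5%.
- **The gain can be modest.** A reader might also infer that ANCOVA is clearly more precise. At an assumed r of 0.7, pairwise power of about 0.84–0.93 with Tukey against more than 0.99 with log-ANCOVA can be produced, but only with raw 3-month values as comparator. Against the defined change outcome, step 3 gives 0.79 against 0.84, and at r = 0.9 there is almost no difference. Log-normal data with an effect on the log scale also favour a log-scale model.
- **It is a condensed article.** Transformation and covariates may be left to a fuller document, and ANOVA matches the sample-size basis. This is fair as regards mere silence. But the pretest gate and the Tukey pairing are stated rules, and the test named between arms is an unadjusted one.
- **Tukey may be meant for ANOVA only.** This is possible, but the sentence does not say so, and the Kruskal–Wallis branch would then have no pairwise method.

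**Conclusion.** The point holds in a limited form and should be corrected; it does not invalidate the trial. Three things are established from the text: the data select the test, a mean-based post hoc test is attached to a rank test, and baseline AMH and FSH are not used as covariates.

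The saving in variance from ANCOVA over change scores is 25%, 15% and 5% at r = 0.5, 0.7 and 0.9. Over 3-month values it is 25%, 49% and 81%. These figures assume equal variances at both visits and an r that the documents do not supply. In large samples ANCOVA is not less precise than either alternative, so it is the safe choice while r is unknown.

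The disagreement rates in step 4 rest on assumed log-normal data and vary with spread and effect pattern. They illustrate the problem and are not bounds. Age should not be counted on for further precision, since nothing in the documents shows how much it explains.

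**What to change.** In section 2.5:

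1. Remove the Shapiro–Wilk gate for the between-arm comparison.
2. For AMH and for FSH, prespecify one ANCOVA of the log 3-month value on arm and log baseline value (age optional). Report Tukey-adjusted pairwise contrasts of the adjusted means as ratios of geometric means with 95% confidence intervals. Tukey's adjustment is appropriate here because the contrasts are between model means.
3. Where Kruskal–Wallis is kept for another outcome, follow it with Dunn's test (Holm-adjusted) or Steel–Dwass.

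**Cost.** The hormone covariates are already in Table 1, so no visit, assay or patient is added, and the planned 120 can stand. Results become ratios instead of raw changes, so section 2.3.1 needs matching wording. The link to change is kept: with log baseline in the model, analysing log change (log 3-month minus log baseline) gives the same arm contrasts as analysing the log 3-month value. A rule for AMH below the assay limit must be written before the data are seen, because a log cannot be taken of an unquantified value.

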### 2.6. Recruitment

Patients meeting the eligibility criteria will be recruited from the Assisted Reproduction Center of Semmelweis University, Hungary. Detailed information about the study will be provided verbally and in writing by the examining physician. Research subjects are informed that in this clinical trial we intend to compare three groups of infertile women. The group receiving only per os complementary therapy, the group receiving per os complementary therapy and walking, and the group receiving per os complementary therapy and a specific exercise program will be tested. We will also inform prospective participants that participation in the research is voluntary and that the anonymized data obtained will be summarized and subjected to statistical analysis. Participation in the study will take approximately 12 weeks.

### 2.7. Implementation

The principal investigator or a designated sub-investigator will input the required data into a web-based allocation system for eligible patients. Subsequently, the system will allocate participants to the three investigated groups. The required data include personal data, demographic data, medical and family history, body composition assessment (weight, height, BMI), menstrual cycle (length and days of menstruation), hormone levels (AMH, FSH, LH, E2, PRL, TSH, vitamin 25-OH-D3), progesterone levels, and the FSFI questionnaire, as shown in Table 1.

## 3. Materials and Equipment

The per os therapy consists of the following supplementation and amounts: daily 3 mg of melatonin (Pharma Nord, Vejle, Denmark) before bedtime in addition to daily intake of 1000 mg of vitamin C (slow release), 400 mg of vitamin E, 2500 IU/day of vitamin D3, and 200 mg of Coenzyme Q10 (Pharma Nord, Vejle, Denmark); and twice daily a preparation containing 2000 mg of myo-inositol, 50 mg of alpha-lactalbumin, and 200 μg of folic acid (Inofolic premium, Exeltis Hungary, Budapest, Hungary). For the rejuvenation exercise, there is no mandatory equipment, although an exercise mat and a pillow or ball are recommended.

## 4. Detailed Procedures

### 4.1. Intervention

The standard dietary supplement/vitamin oral therapy for all three groups includes the intake of a preparation containing myo-inositol + folic acid orally twice a day. Participants in the study are asked to take 3 mg of melatonin before bedtime in addition to daily intake of 1000 mg of vitamin C (slow release), 400 mg of vitamin E, 2500 IU/day of vitamin D3, and 200 mg of Coenzyme Q10.

Combined with the supplement therapy, patients in Arm B will be asked to perform low intensity walking 3 times per week for 1 h each session.

For Arm C (per os therapy and special exercise), our special 70 min moderate-intensity exercise program is available 3 times a week for at least 3 months. This therapeutic exercise program is designed to combine several professional aspects in all exercises including postural correction, pelvic-lumbar stabilization, rehabilitation of the pelvic region, re-education of the pelvic floor muscles, restoration of optimal diaphragm function, dynamic mobilization and stretching exercises, use of the relaxation and therapeutic effects of costo-diaphragmatic breathing, optimization of joint range of motion, and development of balance and coordination. There is a large emphasis on the combination of exercises with relaxation-type exercises of costo-diaphragmatic breathing. The constant attention on breathing helps the patients relax, activates the parasympathetic nervous system, and ensures the strengthening of multiple muscle groups by contraction and relaxation.

The therapeutic movement program begins with a 15 min warm-up focused on teaching active elongation and correct posture, diaphragmatic breathing, hip joint–shoulder joint–thoracic spine mobilization exercises and activating the gluteal group to prepare the pelvic region and the whole body for exercise. The warm-up is followed by a 15 min active core strengthening session, designed to develop the pelvic-lumbar stabilization system and optimize hip joint range of motion, in coordination with proper breathing technique. Proper mobility of the lumbar–pelvic–hip complex and optimal functioning of the core muscles are also necessary for optimal functioning of the pelvic organs (ovaries, uterus). In this session, exercises use coordinated activation of the TVA and pelvic floor muscles along with breathing. The third 15 in section focuses on costo-diaphragmatic breathing in various yoga postures to activate the parasympathetic nervous system, promoting relaxation and stress relief and improving fertility. The other aim of this phase is to restore muscle balance around the pelvis through stretching exercises and to relax the PF through relaxation breathing techniques. The next 15 min session before the cool-down presents the therapeutic objectives of the previous sessions in a complex way, including postural correction, dynamic stretching, and core stabilization exercises, together with correct breathing techniques. Our goal is to compensate for mobility problems due to a sedentary lifestyle, relieve pelvic floor muscles, improve pelvic organ circulation, and correct fertility problems due to restricted hip movements. The final 10 min session is an active pelvic mobilization through dance movements in a vertical position. The aim of this phase is to optimize the movements of the hypomobile lumbar–pelvic–hip complex (LPHC). This is achieved by hip rotations, pelvic tilts, and a combination of these movements. If there is not adequate range of motion in the lumbar spine–pelvic–hip joint, sexual function is significantly affected and limited, and this also has a negative impact on fertility. The stress-relieving effects of music and dance are used to release female energy and mobilize the pelvic girdle.

The workout can be tailored to specific needs by offering multiple levels and incorporating weights. All the exercises will be conducted by a women’s reproductive health physiotherapist.

